### Statistical analysis

The criterion for success of the pilot study is that the definitive trial will be feasible if fidelity to the protocol is at least 70%. We expect protocol fidelity to be ~ 85%. With a sample size of 40, the estimated fidelity of 85% can be estimated with a 95% confidence interval of width 22% (74%–96%). The lower bound of this 95% confidence interval is above the specified level to claim success. If fidelity is less than that specified, reasons will be investigated, and the protocol modified accordingly.

Consistent with published recommendations for pilot studies, we will refrain from a detailed inferential statistical analysis in this pilot study [38]. The sample size is based on the pragmatics of recruitment and the necessities for examining feasibility. Inclusion of HFO_2_ as control group in this pilot is deliberate and will allow realistic examination of recruitment, randomisation, and implementation of interventions.

Categorical variables will be summarised as frequencies (percentage) and continuous measures will be summarised as mean (standard deviation) or median (interquartile range) as appropriate. Binary primary outcome measures for each group will be presented with estimated proportions with 95% confidence intervals to convey precision. Kaplan-Meier curves will be plotted to explore time from enrolment to intubation or death in each group. For outcome measures with continuous repeated measures, within-group change, between-group differences, and differences in rates of change over time will be explored using mixed effects linear regression modelling.

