### Blinding

Due to the nature of the interventions, participants receiving the interventions and the clinicians providing care will be aware of the treatment allocation. During the consent process, participants will be informed of the two interventions and be made aware that both are considered standard of care at the study site.

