### Outcome measurements

Primary outcome.Feasibility◦Recruitment (at least 75% of all eligible patients recruited using approved consent methods)◦Retention (at least 80% of consented pts remaining within study)◦Protocol fidelity (at least 70% of pts in intervention group receiving HFO_2_+iNO for at least 22 h a day (accounting for times where/if iNO is ceased (e.g. transport, investigations, mobility away from the bedspace))◦Data collection procedures (at least 90% of in-person data collected at each study time point)Clinical outcomes (specific timepoints in Fig. 2)Number of patients in each arm progressed to IMV within 28 daysMetHb levels measured via ABGsDaily serum creatinine and urine output levels to monitor renal function and/or renal impairmentChange in PaO_2_ relative to baselineChange in PF ratio relative to baselinePhysiological data◦Respiratory rate (RR)◦SpO_2_◦Systolic blood pressure (SBP)◦Heart rate (HR)Illness severity as estimated by daily sequential organ failure assessment (SOFA) scores [42]Worst daily PF ratioROX index scoresReason for intubation◦Respiratory failure◦Circulatory failure◦Neurological failure◦SurgeryParticipant experience survey (Appendix 1)ICU LOSHospital LOSMechanical ventilation hoursNumber of ventilator free days at day 28Time to mobilisation (minimum classification 4 (standing) on the ICU mobility scale) [43]Best mobility (within first 24 h and during whole length of stay)Daily delirium incidence (Confusion Assessment Method for the ICU (CAM-ICU) score)Retrospective pre-ICU EuroQol 5-Dimension 5-Level (EQ-5D-5L) questionnaireEQ-5D-5L (collected within 5–7 days of discharge from the ICU)Need for anxiolytic and sedative medication during admissionICU mortality

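### Four primary feasibility thresholds are set, but success is judged on fidelity alone, and its precision is computed on 40 patients where the definition covers about 20

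*Protocol article*

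**What the plan says.** Outcome measurements, in the protocol article, lists four components under the primary feasibility outcome, each with its own target:

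- "Recruitment (at least 75% of all eligible patients recruited using approved consent methods"
- "Retention (at least 80% of consented pts remaining within study"
- for protocol fidelity, "at least 70% of pts in intervention group receiving HFO_2_+iNO for at least 22 h a day"
- "Data collection procedures (at least 90% of in-person data collected at each study time point"

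Statistical analysis then gives a single criterion for success, that "the definitive trial will be feasible if fidelity to the protocol is at least 70" per cent. It adds "We expect protocol fidelity to be ~ 85" per cent, and states that with 40 patients the 95% interval is 74% to 96%, so that its lower limit lies above the level needed to claim success. If fidelity falls short, the reasons are to be examined and the protocol changed. Nothing comparable is said for the other three components.

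Design describes the trial as open label. Blinding says participants will be told of the two treatments and that "both are considered standard of care at the study site".

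**The concern.** The pilot exists to decide whether and how to run a multi-centre trial, and Aims makes feasibility its primary purpose. A primary outcome with four numerical targets implies that each bears on that decision. The stated rule uses one of them. If it is applied literally, a trial that cannot enrol, keep or measure its patients can still carry the label feasible.

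The article itself treats the omitted elements as uncertain. Recruitment and consent expects most patients to lack capacity and allows study procedures before consent to continue is obtained. Limitations warns that blood sampling may be uneven and that surveys may be hard to obtain.

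The one component that does decide has a second problem. It is defined in one arm, but its precision is worked out as if both arms contributed.

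**Working it through.** **1. The two sections side by side.**

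| Component | Target | In the success rule? | Consequence of a miss stated? |
|---|---|---|---|
| Recruitment | 75% of eligible | No | No |
| Retention | 80% of consented | No | No |
| Fidelity | 70% of intervention group | Yes | Yes |
| Data collection | 90% at each time point | No | No |

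**2. What the rule lets through.** Take 40 enrolled and 20 per arm (Sample size), with all 40 counted as consented.

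- Meeting the recruitment target needs at most 53 eligible patients (40/0.75 = 53.3).
- Meeting the retention target needs 0.80 × 40 = 32 retained.
- Meeting the fidelity target needs 0.70 × 20 = 14 patients.

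A pilot with 40/100 = 40% recruited, 24/40 = 60% retained, incomplete data and 14/20 = 70% fidelity misses three targets and passes the rule.

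**3. How often the rule and the targets could disagree.** The true rates here are assumptions, except 85% fidelity, which is the article's expectation. Binomial tails:

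- P(at least 14 of 20 | 0.85) = 0.978, the chance that the rule is met.
- P(at least 32 of 40) for true retention of 60%, 70%, 80% and 90% = 0.006, 0.111, 0.593 and 0.985.

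At 70% retention, the chance that both targets are met is 0.978 × 0.111 = 0.109 if the two are independent. Whatever the dependence, it lies between 0.978 + 0.111 − 1 = 0.089 and 0.111. The rule would still report success with probability 0.978.

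**4. The article's interval, reproduced.** Wald: p ± 1.96 × √(p(1 − p)/n), with p = 0.85 and n = 40. The half-width is 1.96 × √(0.1275/40) = 0.111, giving 73.9% to 96.1%, width 22.1%. This matches the stated 74% to 96%, width 22%. On the same 40 patients, Wilson gives 70.9% to 92.9% and the exact interval for 34/40 gives 70.2% to 94.3%.

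**5. The same check on the defined denominator.** With 17/20 = 85%:

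| Method | Lower | Upper |
|---|---|---|
| Wald | 69.4% | 100.6% |
| Wilson | 64.0% | 94.8% |
| Exact | 62.1% | 96.8% |

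All three lower limits are below 70%. The Wald shortfall is small: its lower limit would reach 70% at n = 1.96² × 0.1275/0.15² = 21.8, that is, 22 patients, which simple randomisation could supply by chance. However, the Wald upper limit passes 100% at n = 20, so that method is unsuitable at this size. With 20 patients the exact lower limit is 68.3% for 18/20 and 75.1% for 19/20, so 19 of 20 would be needed to clear 70%.

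**The case against.** The strongest reply is that the other three targets are not discarded. They remain primary outcomes with numerical thresholds, binary primary measures are to be reported with 95% intervals, the feasibility results are meant to shape the later protocol, and the monitoring committee may recommend changes or stopping. All of that stands, and a reader who inferred that recruitment, retention and data collection will be ignored would go too far. None of these provisions, however, alters the stated success criterion, and a missed target could be reported beside a declaration of feasibility.

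A second reply is that the success sentence refers to fidelity to the protocol in general and uses n = 40, so it may intend both arms. That reading is open. But the only definition given is for the intervention group, and fidelity among controls is defined nowhere. On either reading the two sections need reconciling.

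A reader might also infer, from the open-label design and the statement on local standard of care, that many controls will receive inhaled nitric oxide and that the treatment contrast will be badly diluted. The article does not support that. It predicts no such use, the sentence in Blinding describes what participants are told, and there is neither a crossover rate nor an expected effect of inhaled nitric oxide from which to size any dilution. What remains is that such use is possible and that no success measure counts it.

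Finally, requiring all four targets is not the only defensible rule. Since data collection must reach 90% at every time point, one poor time point could withhold the label. A graded rule would meet that objection.

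**Conclusion.** The concern holds as a conflict between two sections of the article. Three of the four primary thresholds have no stated place in the success rule, so the rule can report success when all three are missed. This rests on the text alone; the probabilities in the working illustrate it under assumed true rates.

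The numerical part also holds. The interval of 74% to 96% is correct for 40 patients but does not match the defined denominator of about 20, where an observed 85% has an exact interval of about 62% to 97%. The assurance that the lower limit exceeds 70% fails there. If success means only a point estimate of at least 70%, this weakens the supporting argument and leaves the decision unchanged. If the lower limit is meant to decide, the expected 85% would not suffice.

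Control-arm use of inhaled nitric oxide is a gap worth closing by measurement, not a predicted failure.

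**What to change.** - **Decision rule.** Replace the success sentence in Statistical analysis: the definitive trial is judged feasible as designed only if all four thresholds in Outcome measurements are met, and a miss on any one leads to modification of that element before proceeding. A pre-specified go/amend/stop rule for each threshold would also serve.
- **Fidelity denominator.** Reconcile the two sections, state that fidelity is assessed in the intervention arm, and restate its interval on that arm's number, preferably by an exact method. Say whether the point estimate or the lower limit decides.
- **Control arm.** Report the proportion of controls given any inhaled nitric oxide, with its exact interval, as a separate measure. Do not pool it with intervention-arm fidelity: 20/20 compliant controls plus 8/20 compliant intervention patients gives 28/40 = 70%, a pass with only 40% fidelity where it matters.

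The cost is a few sentences and one control-arm item (given or not, and when), which should be obtainable from the electronic records already in use. The drawback is that success becomes harder to claim and the stated precision less favourable. Trial status says recruitment had not begun at the time of writing. The change should be made before recruitment or, if it has since started, before any feasibility results are examined.

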## Methods

### Design

This will be an open label, 1:1 parallel group, single-centre, pilot (*n* = 40) randomised controlled trial. The study protocol has been reported using the Standard Protocol Items: Recommendations for Interventional Trials (SPIRIT) statement guidelines [39], and the associated publication from the study will be reported in accordance with the CONSORT extension for randomised pilot and feasibility trials [40]. The SPIRIT figures (Figs. 1 and 2) outline the schedule of enrolment, interventions, and assessments [39].

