### Sample size

As a pilot trial, it is not required to be powered to detect statistical significance. A sample of 40 eligible patients will be recruited over a period of 12–18 months. Assuming the proportion of patients who progress to IMV is 0.38 [24], a sample of 20 per group will produce an exact 95% CI width of 0.44.

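### The 74%–96% precision figure for protocol fidelity uses all 40 patients, but fidelity is defined only in the intervention arm (about 20), where the lower bound at 85% falls below 70%

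*Protocol article*

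**What the plan says.** Under Outcome measurements, protocol fidelity is one of four feasibility measures that form the primary outcome. Its target is "at least 70% of pts in intervention group receiving HFO_2_+iNO for at least 22 h a day", with allowance for times when the gas is stopped, such as transport. This is the only definition of fidelity in the article, and control patients receive high-flow oxygen without nitric oxide.

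The Statistical analysis section makes this measure decisive: "the definitive trial will be feasible if fidelity to the protocol is at least 70" per cent. It gives an expected value ("We expect protocol fidelity to be ~ 85" per cent) and then the precision: "With a sample size of 40, the estimated fidelity of 85% can be estimated with a 95% confidence interval of width 22% (74%–96" per cent). It concludes: "The lower bound of this 95% confidence interval is above the specified level to claim success".

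The Design section describes an "open label, 1:1 parallel group, single-centre, pilot" trial of 40 patients. The Sample size section works per arm for the intubation outcome: "a sample of 20 per group will produce an exact 95% CI width of 0.44".

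**The concern.** The precision statement and the definition use different denominators. Fidelity is a proportion of intervention-arm patients, so with 1:1 allocation of 40 its denominator is about 20. Using 40 understates the uncertainty.

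This interval is the only numerical support offered for the pilot's success criterion. A reader planning the definitive trial would take from it that the expected result, 85% fidelity, would exclude values below 70%. If the interval belongs to a denominator twice the real one, that reassurance is not available. The lower-bound sentence also links claiming success to the confidence limit, while the criterion itself is worded as a simple threshold. At 85% observed fidelity in 20 patients, the threshold is met but the lower bound does not clear it.

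**Working it through.** **Inputs.** Expected fidelity p = 0.85, threshold 0.70, 95% confidence and n = 40 (Statistical analysis). Denominator restricted to the intervention group (Outcome measurements). 1:1 allocation (Design) and 20 per group (Sample size). z = 1.96.

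**Step 1: reproduce the stated interval.** Wald: p ± z·√(p(1−p)/n).
- n = 40: √(0.85 × 0.15 / 40) = 0.0565, and 1.96 × 0.0565 = 0.1107.
- Interval 73.9% to 96.1%, width 22.1 points.

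This matches the stated 74% to 96% and width of 22%. Other methods for 34/40 give different limits (Wilson 70.9% to 92.9%, exact 70.2% to 94.3%), so the figure is a Wald interval on all 40 patients.

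**Step 2: same quantity, defined denominator (17/20 = 85%).**
- Wald: √(0.85 × 0.15 / 20) = 0.0798, and 1.96 × 0.0798 = 0.1565. Interval 69.4% to 100.6%, truncated to 100%. Width 31.3 points before truncation and 30.7 after.
- Wilson: centre (p + z²/2n)/(1 + z²/n) = (0.85 + 0.0960)/1.1921 = 0.7936. Half-width z·√(p(1−p)/n + z²/4n²)/(1 + z²/n) = 1.96 × √(0.006375 + 0.002401)/1.1921 = 0.1540. Interval 64.0% to 94.8%, width 30.8 points.
- Exact (Clopper-Pearson): lower limit is the 2.5% point of Beta(17, 4), upper limit the 97.5% point of Beta(18, 3). Interval 62.1% to 96.8%, width 34.7 points.

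All three lower limits are below 70%.

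**Step 3: what would put the lower limit above 70% with 20 patients?**

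| Method | Smallest observed count | Lower limit | Chance if true fidelity is 85% |
|---|---|---|---|
| Wald | 18/20 (90%) | 76.9% | 40% |
| Wilson | 19/20 (95%) | 76.4% | 18% |
| Exact | 19/20 (95%) | 75.1% | 18% |

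**Step 4: sensitivity to arm size.** The article specifies simple random allocation, so the intervention arm is not fixed at 20. Its central 95% range is 14 to 26 of 40. By Wald at 85%, the lower limit passes 70% when n > 0.85 × 0.15 × (1.96/0.15)² = 21.8, so with 22 or more patients (21 gives 69.7%, 22 gives 70.1%). The chance of an arm of at least 22 is about 32%.

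**The case against.** Several points on the other side are fair.

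- *The arithmetic is right for 40 patients, and by the protocol's own method the miss at 20 is small.* Both are true. The Wald lower limit is 69.4% against 70%. The larger shortfalls come from Wilson and exact intervals, which the article does not promise for fidelity; its exact interval concerns intubation. What stands is that the width is wrong by about 9 points or more by any of the three methods, and that the lower-bound sentence fails by all three.
- *Using Wald is itself an error.* A reader might infer this, but it changes no conclusion at 40, where the exact lower limit is 70.2% and still above the threshold. The defect is the denominator.
- *Fidelity may have been meant for both arms.* The Statistical analysis section does not name an arm and gives the control group a role in examining how the interventions are implemented. That is possible, but no two-arm measure is defined, so the two sections still have to be reconciled.
- *This is a pilot without formal inference.* Agreed, and missing the target leads to investigation and modification of the protocol, not to a failed test. The point is a precision statement that the article makes itself, not a lack of power.
- *The criterion is a point-estimate threshold, so it is unaffected.* That is the more natural reading, because all the feasibility targets are worded as minimum percentages. The lower-bound sentence speaks of claiming success, however, and leaves room for the other reading.

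**Conclusion.** The precision statement does not fit the measure as the article defines it. For an observed 85% in 20 intervention patients, the 95% interval is about 62% to 97% (exact), 64% to 95% (Wilson) or 69% to 100% (Wald, truncated), against the stated 74% to 96%. The sentence that the lower bound exceeds the success level is not true at the planned arm size: just barely by Wald, clearly by the other two methods.

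This rests on the Outcome measurements definition being the operative one and on an arm of about 20. A chance imbalance giving 22 or more intervention patients would rescue the sentence by Wald, but a planning statement cannot rely on that.

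A reader might go further and infer that the trial cannot show fidelity above 70%. The figures do not support that. If true fidelity is 85%, the lower limit would still exceed 70% with probability of about 18% (exact or Wilson) or 40% (Wald). Nor does the point undermine the 70% threshold, the sample size or the design, none of which depends on this interval.

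**What to change.** In the Statistical analysis section, replace the interval with one for the intervention arm. For example: *With about 20 patients in the intervention arm (the actual number will vary under simple randomisation), an observed fidelity of 85% (17/20) would have an exact 95% confidence interval of 62% to 97%.* Name the interval method. Delete the lower-bound sentence. State that the 70% criterion is judged on the observed percentage in the intervention arm, reported with its confidence interval. Keep the threshold as a percentage: simple randomisation yields exactly 20 in the arm only about 13% of the time, so a fixed count such as 14 of 20 would usually not match the real denominator.

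Alternatively, if 40 was intended, define under Outcome measurements what fidelity means in the control arm, so that both sections describe one measure on all patients.

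The first option costs only wording. The second also requires a control-arm definition and the data to support it. Neither needs extra patients. The price of the first is that the stated precision becomes visibly less favourable.

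### The 70% fidelity criterion is supported by a 95% lower-bound argument that it does not apply and that an intervention arm of about 20 does not deliver

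*Protocol article*

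**What the plan says.** The Statistical analysis section of the protocol article opens with the pilot's success criterion: "The criterion for success of the pilot study is that the definitive trial will be feasible if fidelity to the protocol is at least 70" per cent. The Outcome measurements section gives the same threshold and fixes the denominator: "at least 70% of pts in intervention group receiving HFO_2_+iNO for at least 22 h a day". The consequence of a miss is tied to the same level: "If fidelity is less than that specified, reasons will be investigated, and the protocol modified accordingly".

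Between the criterion and that consequence, the Statistical analysis section takes an expected fidelity of about 85%, attaches a 95% interval of 74% to 96% for a sample of 40, and adds: "The lower bound of this 95% confidence interval is above the specified level to claim success".

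The same section says that binary primary outcomes will be shown as proportions with 95% intervals to indicate precision, and that detailed inference will be avoided. The Sample size section gives 20 patients per group. Allocation is 1:1 by simple randomisation.

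**The concern.** Two different comparisons with 70% stand side by side. The criterion and the consequence of a miss compare fidelity itself with 70%. The text says neither that this is the observed proportion nor that it is a confidence limit, but the observed proportion is the natural reading. The supporting sentence compares the lower limit of a two-sided 95% interval with 70% and links that comparison to claiming success. This is a one-sided 2.5% standard of evidence, and nothing in the criterion requires it.

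A reader of the supporting sentence would expect a declared success to mean that true fidelity below 70% has been ruled out. A success under the stated criterion need not mean that. Of the four feasibility targets, fidelity is the one singled out as the criterion for success. The Aims section says that the feasibility results will inform the budget and protocol of a multi-centre trial, so what a success can be said to show matters.

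**Working it through.** **Inputs.** From the Statistical analysis section: threshold 70%, expected fidelity 85%, printed n = 40. From Outcome measurements: fidelity is measured in the intervention group. From Sample size: 20 per group.

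**1. The plan's own figure.** Wald interval: p ± 1.96 × √[p(1 − p)/n].
- With p = 0.85 and n = 40: 0.85 ± 1.96 × √(0.1275/40) = 0.85 ± 0.111, or 73.9% to 96.1%, width 22.1 points. This reproduces the printed 74% to 96%.
- At 34/40 the Wilson lower limit is 70.9% and the exact (Clopper-Pearson) limit 70.2%. With n = 40 the sentence holds by all three methods, although narrowly by the last two.

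**2. The same calculation in the intervention arm, n = 20, 17/20 = 85%.**
- Wald: 0.85 − 1.96 × √(0.1275/20) = 0.85 − 0.156 = 69.4%.
- Wilson: 64.0%.
- Exact: the 2.5% quantile of Beta(17, 4), which is 62.1%.

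All are below 70%.

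**3. Sensitivity to arm size.** Simple randomisation need not give exactly 20. At an observed 85%:
- the Wald limit exceeds 70% when n > 1.96² × 0.1275/0.15² = 21.8, so from 22 patients;
- the Wilson limit, which inverts the score test, exceeds 70% when n > 1.96² × 0.21/0.15² = 35.9, so from 36 patients.

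The Wald result at 20 is therefore a near miss. The Wilson result is not.

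**4. Smallest count that meets each standard, and the chance of meeting it at a true fidelity of 85%** (upper tail of the binomial distribution):

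| Standard | n = 20: count | n = 20: chance | n = 40: count | n = 40: chance |
|---|---|---|---|---|
| Observed proportion at least 70% | 14 | 97.8% | 28 | 99.6% |
| Wald lower limit above 70% | 18 | 40% | 33 | 76% |
| Exact lower limit above 70% | 19 | 18% | 34 | 61% |

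The Wald limit is 76.9% at 18/20. The exact limit is 68.3% at 18/20 and 75.1% at 19/20. At 14/20, the smallest success, the exact limit is 45.7%.

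**5. How often the two standards disagree.** Disagreement runs one way only: the observed proportion passes and the lower limit fails.
- n = 20: counts 14 to 17 (Wald) or 14 to 18 (exact). At a true 85% the probability is 57% or 80%.
- n = 40: counts 28 to 32 (Wald) or 28 to 33 (exact), which is 5 or 6 of the 13 passing counts. At a true 85% the probability is 24% or 39%. It exceeds 50% only for true fidelity of about 70% to 80%.

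**The case against.** The strongest reply is that the plan states only one decision rule. The criterion, its repetition among the outcomes and the consequence of a miss all use fidelity of at least 70%. The lower-bound sentence refers to one hypothetical interval, at 85% and n = 40, and is a planning remark about precision. The section's statements that intervals show precision and that detailed inference is avoided point the same way. This stands. A reader might infer that the protocol sets two rules in open contradiction, but the text does not go that far: it never says that success will be judged on the observed lower limit.

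A reader might also infer that the two standards give opposite answers over most plausible results whatever the denominator. That is not supported either. With the printed 40, the expected 34/40 meets both standards and disagreement at 85% is 24% to 39%. The larger figures belong to the arm of about 20, and they depend on the interval method. The printed interval is Wald, so quoting only the exact results would overstate the gap. Nor is the lower-bound standard out of reach. It is harder to meet, with a chance of 18% to 40% at n = 20 and 61% to 76% at n = 40.

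Finally, correcting the denominator alone would force the sentence to be rewritten. That is true, but it would not settle which quantity decides. Read purely as planning, the sentence still offers an assurance that a success at 14/20 does not carry.

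**Conclusion.** The point holds as a wrong support for the success criterion and as an ambiguity about what a success shows. It is not a contradiction between two declared rules. The criterion is most naturally met at 14/20. The lower-bound assurance needs 18/20 or 19/20 and is not met at the expected 17/20 by the Wald, Wilson or exact method. At a true fidelity of 85%, the chance of meeting the criterion is 98%, and the chance of also having the assurance is about 40% (Wald) or 18% (exact).

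This rests on three assumptions: that the criterion refers to the observed proportion, which the text implies but does not state; that the denominator is the intervention group, as the outcome definition says; and that this group numbers about 20. By the Wald method, an arm of 22 or more would put the lower limit at an observed 85% just above 70%. By Wilson it would take 36.

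**What to change.** - State that the criterion is met when the observed proportion in the intervention group is at least 70%.
- Delete the lower-bound sentence, or rewrite it and the interval before it with the intervention-arm denominator, naming the interval method. With 20 patients it would have to say that the lower limit at the expected 85% is below 70%.
- Where the 95% interval already planned for reporting includes values below 70%, word the conclusion as target met, with true fidelity below 70% not excluded.
- Optionally, give the chance of passing with about 20 patients: 25%, 61% and 98% at true fidelity of 60%, 70% and 85%.

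This changes wording only, with no added patients or data. The article reports that recruitment had not begun when it was written; the wording should be settled before fidelity data are seen. The cost is that a success is described as weaker evidence than the present text suggests.
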